### Baseline assessment and randomization

#### Screening

Once a potentially eligible participant is identified, the interviewer from the telephone survey firm confirms the participant’s age and administers the CIDI-SFMD and the sex-specific prediction algorithms. Interviewees who are in a MDE or are below the risk thresholds based on the risk calculators, are excluded. Individuals with MDE are encouraged to contact family doctors and information about local mental health resources is provided. For those who are at low risk, the web site of the MVRPs is provided so they may monitor their risk in the future.

#### Baseline assessment

In eligible participants, the interviewer administers the K10, SSUS, and asks questions about absenteeism and perceived risk of MDE. Baseline assessment takes 20 to 25 min.

*Randomization* is carried out in men and in women. The telephone survey firm uses a survey software tool built by Voxco. The tool contains a random number generator which randomly creates a digit when the telephone script reads the function. The firm confirmed that this is comparable to the traditional method of using sealed opaque envelopes.

### Intervention and control

For the participants in the intervention group, the personalized risk is disclosed and the interviewer informs the participants that they will be contacted again at 6 months and 12 months. The interest in receiving such personalized depression information has been confirmed by our recent pilot study using the same sampling method. Our pilot data (*n* = 200) showed that 100% of high-risk individuals were interested in knowing their risks. Participants in the intervention group are also informed that some may be contacted in 1 month for a 30-min qualitative interview. A package including the following materials is mailed to intervention participants: (1) thank-you letter, (2) general information about MDE, (3) self-help strategies [15] and a summary of research evidence supporting the effectiveness of self-help strategies, and (4) $20 incentive as appreciation of their participation. For participants in the control group, the interviewer informs them that they will be contacted again at 6 and 12 months. Their personal risks will be provided at the 12-month interview. They receive the same package as those in the intervention group.

### Blinding and follow-up assessments

The telephone survey firm securely transfers encrypted baseline data to the PI on a weekly basis. The group assignment data are transferred in a separate file. The follow-up assessments are conducted at the telephone interview laboratory at the University of Ottawa Institute of Mental Health:
One month before the scheduled follow-up interviews, letters are sent to participants to remind them of the upcoming interview.After the 12-month interview, participants’ group status is linked with interview data by study ID numbers.

Investigators are blinded to participants’ group status. The interviewers who conduct randomization, are not involved in follow-up interviews. The interviewers who conduct the follow-up interviews in Ottawa do not have access to participants’ group status. Given our description of study objectives, participants may know their group status. Therefore, it is possible that some participants in the control group may try to find more information about personalized depression risk. At the follow-up assessments, we will ask if they have used any risk prediction tools over the study period. At the follow-up assessments, if participants develop a MDE, they are encouraged to contact family doctors and information about local mental health resources is provided.

### Qualitative interviews

To obtain in-depth information about how disclosing personalized depression risk affects participants’ decision processes, mental health and health behaviors, we conduct two rounds of qualitative interviews via telephone, 1 month after these participants receive the personalized depression risk and at 12 months. Each includes an initial random sub-sample of 20 men and 20 women from the intervention groups. The qualitative interviews strengthen our study as we will use the findings to “triangulate” our quantitative results and to guide interpretation of the quantitative results [22]. The interviews are audio recorded. Qualitative interviews are transcribed verbatim then analyzed inductively for themes. Our analysis follows the interpretive practices of constant comparison and attempt to uncover patterns both within and between interviews [23]. Nvivo 10 software is used to support thematic analysis. We expect to achieve theoretical saturation with the initial sample of 20. However, if new themes continue to emerge in our final interviews, we will interview additional participants until no new themes emerge.

### Data monitoring

The principal investigator (PI) and the research coordinator (RC) are responsible for daily operation of the project, and monitoring data collection, data quality and potential adverse events. The PI and RC report to the research team at teleconferences held every 3 months. The funder plays no role in the process of data monitoring.

### Adverse events/harm

Our study population are individuals who are not in an episode of depression, but are at high risk. The data collection is conducted via telephone. Therefore, the possibility of physical injuries is minimum. In the circumstance that the participant may need mental health services, the interviewers are instructed to encourage the individual to seek professional help, and provide information about local mental health resources. If an unintended adverse event occurs, the ERB will be immediately notified and the event will be jointly reviewed by the board and the research team.

### Statistical analysis

All analyses will be carried out in men and in women separately, and by group assignment. We will perform an intention-to-treat analysis based on randomization. Each outcome will be analyzed with a separate regression model that includes intervention assignment and demographics, history of MDE and predicted risk at baseline as covariates.

Mixed ANOVA with a random intercept will be used to examine the effect of disclosing personalized depression risk information on changes in the SSUS scores, K10 scores and number of days off work. The mixed model will enable the repeated measures to be included in a single analysis and so that data from subjects not followed for the full year can be included. We expect no significant differences between the groups in changes of K10 scores and absenteeism at 6 and 12-month, i.e., disclosing the risk information does not lead to psychological and functioning harms. To examine the effect of risk disclosure on accuracy of perceived risk, we will first subtract participants’ perceived risk from the predicted risk. Positive values of the difference indicate underestimation of risk; negative scores indicate overestimation. We will recode difference scores into a dichotomous variable (≤10% vs > 10%) [13, 14], indicating whether perceived risk is “close” to the predicted risk. The proportions of accurate risk perception at baseline 6- and 12-month will be estimated and compared. Stratified analyses by demographic variables, history of MDE, baseline predicted risk levels will be conducted. Additionally, we will conduct the same analyses in participants who do not have missing outcome data (the completers).

Interim analysis will be conducted after 6-month follow-up. If the intervention group has a significantly higher incident proportion of major depression, and/or of suicidal behaviors, controlling for baseline covariates, than the control group, a team meeting involving staff of ethics review board will be held to review the results and determine whether the trial will be terminated.

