### Recruitment

The target population for future preventive studies is high risk people in the general population. For the proposed study, we are recruiting eligible participants using the random digit dialing method (RDD). We have used the RDD for recruitment in other longitudinal studies [9, 10] and an ongoing national RCT [11]. Recruitment, screening, baseline assessment and randomization are completed by a telephone survey firm that has access to household telephone and validated cell phone numbers across the country. The recruitment and randomization procedures and questionnaire were pilot tested in 20 eligible participants, using a cognitive interviewing method [12].

A random sample of landline and cell phone numbers are selected. When a household is reached, the person who is 18+ years is assessed for eligibility. If a household has 2+ persons aged 18+ years, one is randomly selected. The interviewers explain the study objectives and procedures and answer questions. Potential participants are ensured confidentiality, that participation is voluntary and that they may withdraw at any time. Oral consent is obtained before assessment of eligibility by asking the question: “Do I have your consent to begin the survey?” The answer of “yes” and continued participation is deemed to be informed consent. The Research Ethics Board formally approved this consent.

Outcome measures are assessed at baseline, 6 and 12-month.

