### Sample size calculation

A RCT on the impact of e-mail promotion of self-help strategies for depression [15] showed that participants in the intervention group had modest but significant improvement in SSUS scores than those in the control group by a mean of 2.6 points, effect size d = 0.40. Assuming our study will achieve similar effect size, 258 participants (129 in each group) are needed to achieve the power of 0.80 at the α level of 0.05. The sample size calculation was done using STATA version 13. Assuming that the 12-month follow-up response rate is 75% with $20 incentive [10], we should recruit at least 344 participants (172 in each group) at baseline. Because the study will be carried out by sex separately, we proposed to recruit 350 men and 350 women who meet the inclusion criteria at baseline.

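### The models for change in SSUS, K10 and days off work neither adjust for the outcome's own baseline nor say that baseline arm means are held equal, which costs precision, above all in the K10 harm comparison

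*Protocol article*

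**What the plan says.** Under Statistical analysis, the article states that each outcome has its own regression model that "includes intervention assignment and demographics, history of MDE and predicted risk at baseline as covariates". The next paragraph gives the model for the continuous outcomes: "Mixed ANOVA with a random intercept will be used to examine the effect of disclosing personalized depression risk information on changes in the SSUS scores", with K10 scores and number of days off work named in the same sentence. It adds that "The mixed model will enable the repeated measures to be included in a single analysis", so that people not followed for the full year still contribute.

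The baseline values exist. Under Recruitment: "Outcome measures are assessed at baseline, 6 and 12-month". Under Baseline assessment: "In eligible participants, the interviewer administers the K10, SSUS, and asks questions about absenteeism and perceived risk of MDE".

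The Statistical analysis section also says what is expected of the harm outcomes: no significant group difference in change in K10 or absenteeism at 6 and 12 months, which it equates with disclosure doing no psychological or functional harm.

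**The concern.** A person's own baseline score is usually the best single predictor of the later score on the same scale. The listed covariates do not include it, and the effect is defined on change. In the usual mixed ANOVA (group, time, group by time), baseline is one of the repeated responses and each arm has its own free baseline mean. The group-by-time contrast is then a difference in change and carries the full noise of the chance baseline difference between arms. Randomization makes the true baseline difference zero. A model that uses this, by adjusting for baseline or by holding the baseline means equal, has a smaller variance with the same data.

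For SSUS the cost is some power. For K10 the stakes are higher. The second research question is whether disclosure harms mental health, and the plan treats absence of significance as absence of harm. Under that reading, every loss of precision favours the expected conclusion. The trial is sized on SSUS alone, and men and women are analysed separately, so the harm comparison rests on the smaller, single-sex sample.

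**Working it through.** **Inputs from the article.** Allocation 1:1; 350 recruited per sex; 12-month response 75%; SSUS effect "by a mean of 2.6 points, effect size d = 0.40"; power 0.80; alpha 0.05 (taken as two-sided, since sidedness is not stated). Completers per arm: 350 × 0.75 / 2 ≈ 131, leaving 175 − 131 = 44 per arm seen only at baseline.

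**Assumptions.** The baseline to follow-up correlation rho is not given, so 0.3 to 0.8 is shown. Variances are taken as equal across visits. Rho may differ between the three outcomes, and for days off work, a count, the formula is only a guide.

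**The plan's own figure.** n per arm = 2(1.96 + 0.84)² / 0.40² gives 99 (about 100 by t-test), not the stated 129. With 129 per arm, power at d = 0.40 is about 0.89; 129 would fit d = 0.35 at power 0.80. The attrition step reproduces: 258 / 0.75 = 344. The stated number is larger than its inputs require, which matters here only because it leaves some reserve for SSUS.

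**Variance of the arm contrast at one follow-up visit, in units of the score variance.**

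- Difference in change (free baseline means): 2(1 − rho).
- Baseline-adjusted (or equal baseline means): 1 − rho².
- Ratio, adjusted to change: (1 + rho)/2. Share of variance lost: 1 − (1 + rho)/2 = (1 − rho)/2.

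A generalised least squares calculation on a three-visit random-intercept model confirms both forms with complete data. It was repeated with 131 completers and 44 baseline-only participants per arm.

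| rho | Change | Adjusted | Share lost, complete data | Share lost, 25% baseline-only |
|---|---|---|---|---|
| 0.3 | 1.40 | 0.91 | 35% | 29% |
| 0.4 | 1.20 | 0.84 | 30% | 24% |
| 0.5 | 1.00 | 0.75 | 25% | 20% |
| 0.6 | 0.80 | 0.64 | 20% | 16% |
| 0.7 | 0.60 | 0.51 | 15% | 12% |
| 0.8 | 0.40 | 0.36 | 10% | 8% |

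Example for the last column at rho = 0.5: variance 0.01431 with free baseline means and 0.01145 with equal ones; 1 − 0.01145/0.01431 = 20%.

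**SSUS power at d = 0.40, 131 completers per arm.** SE = √(2V/131), power = Φ(0.40/SE − 1.96), with V from the table. Change against adjusted: 0.78 and 0.92 (rho 0.3), 0.84 and 0.94 (0.4), 0.90 and 0.96 (0.5), 0.99 and 0.995 (0.7).

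**K10, illustration.** Suppose disclosure truly raises K10 by 0.30 SD (an assumption, not a figure from the article). By the same formula, the chance of a non-significant result, change against adjusted, is 40% and 25% (rho 0.4), 32% and 20% (0.5), and 12% and 8% (0.7). At rho 0.5: SE = √(2 × 1.00/131) = 0.124 against √(2 × 0.75/131) = 0.107.

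**The case against.** The strongest reply is that baseline is not discarded. Outcomes are measured at three visits and the repeated measures go into one analysis, so baseline most naturally enters as a response. If the arms' baseline means are held equal there, nothing is lost. Whether they are is a term-level detail that a condensed article may leave to a fuller document. This stands as far as it goes: a reader who infers that the plan ignores the baseline scores goes beyond the text. But the article does state a covariate list and an effect defined on change. In its usual form that combination has free baseline means, and nothing in the text points to the constrained form.

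The second reply is that the cost is modest. That also stands for SSUS: at d = 0.40, change-score power exceeds 0.80 for rho of 0.4 or more. Predicted risk and history of MDE may recover some of the loss, and baseline-only participants shrink it. None of this covers K10, for which no sample size was set.

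A reader might also infer three stronger points that the document does not support:

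- That, with no assignment-by-time term listed, the effect is averaged over a baseline visit where it must be zero and so shrinks to two thirds. The plan compares changes at 6 and 12 months, and the K10 description speaks of comparing change over time between groups. Both imply a group-by-time contrast.
- That the random intercept must give way to an unstructured covariance. That is a separate modelling preference, and nothing in the article shows the random intercept to be inadequate.
- That a single percentage loss can be quoted as fact. It depends on rho, which is not given.

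**Conclusion.** The point holds as one of precision. As written, the analysis of change in SSUS, K10 and days off work omits the outcome's own baseline from its covariates and does not say that baseline means are constrained. In its usual form it loses a variance share of (1 − rho)/2 against an analysis that uses baseline fully. Over the assumed rho range this is about 10% to 35% with complete data. Standard errors would then be 5% to 19% smaller with adjustment (√0.90 = 0.949; √0.65 = 0.806). At rho 0.7 to 0.4 with a quarter of each arm seen only at baseline, the variance share is about 12% to 24%. These figures assume equal variances and take no account of what the listed covariates recover.

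The difference in change is not biased on average over randomization, and the planned SSUS power is not shown to fail unless rho is near 0.3. The reason to act is the K10 comparison, where imprecision would be read as reassurance. If the intended model already holds the baseline means equal, the only defect is that the article does not say so.

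**What to change.** Keep the mixed model and the listed covariates, and add one of two statements:

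- Baseline, 6- and 12-month scores are the response, with the two arms' baseline means constrained to be equal. This keeps participants seen only at baseline in the analysis, in line with the stated aim of including people not followed for the full year.
- The 6- and 12-month scores are the response, with the baseline score as a covariate and arm, time and arm-by-time terms. Participants with no follow-up score then drop out of the model.

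In either case, report the arm difference with its confidence interval at 6 and at 12 months, separately for men and women as planned.

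The cost is model wording only. The baseline scores are already collected, and neither sample size nor visits change. The choice should be recorded before group status is linked to the interview data, which the Blinding and follow-up assessments section places after the 12-month interview.

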## Methods/design

Given the background, the aim of the proposed randomized controlled trial is to answer the following research questions: (1) Does disclosure of personalized depression risk information promote high-risk individuals to take preventive actions? The effect of risk prediction may be maximized if these individuals actively engage in early prevention. (2) Will disclosure of personalized depression risk information negatively affect high-risk people’s mental health status? To safely implement the prediction algorithms, we need to ensure that the disclosure will not lead to increased psychological distress.

This study is a mixed-methods randomized controlled trial (RCT) with an embedded qualitative component. The RCT has one intervention arm (receiving personalized depression risk information) and one control arm (1:1). The target population are individuals in the community who are at high risk of major depression. The personalized depression risk is generated using the sex-specific MVRPs for MDE that we developed in Canadians aged 18+ years old [4]. Thus, the inclusion criteria are:
no MDE at baseline, or if had a MDE in the past 12 months, the individuals were in full remission for at least 2 months before the interview (see below the question),aged 18+ years,at high risk of MDE based on the algorithms (predicted risk of 6.5% + for men and of 11.2% + for women) [4],agreement to be contacted for follow-up assessments, andno language barriers to English or French.

The status of remission was assessed by the question: “In the past 2 months or longer, has your mood been much improved or back to normal AND you DIDN’T have the symptoms of.....?” This question was adopted from the US National Epidemiological Survey on Alcohol and Related Conditions [7]. Because the prediction algorithms are sex-specific, we are recruiting 350 men and 350 women at baseline. After baseline assessment for eligibility, participants are randomized into intervention and control groups, in men and women separately.

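### Taken alone, the planned random intercept assumes equal correlation between all visits; if correlation fades with time, the 12-month change contrast has too small a standard error

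*Protocol article*

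**What the plan says.** All of this is in the protocol article; no separate analysis plan is at hand.

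- **Model** (Statistical analysis): "Mixed ANOVA with a random intercept will be used to examine the effect of disclosing personalized depression risk information on changes" in SSUS scores, K10 scores and days off work. The stated reason is that "The mixed model will enable the repeated measures to be included in a single analysis", so that people with partial follow-up still contribute.
- **Visits** (Recruitment): "Outcome measures are assessed at baseline, 6 and 12-month".
- **Covariates** (Statistical analysis): "intervention assignment and demographics, history of MDE and predicted risk at baseline as covariates". The outcome's own baseline value is not listed, which fits a model in which baseline is one of three repeated measures.
- **What is interpreted** (Statistical analysis): "We expect no significant differences between the groups in changes of K10 scores and absenteeism at 6 and 12-month". The section takes this to mean that disclosure does no psychological or functional harm.
- **Population per model** (Statistical analysis): "All analyses will be carried out in men and in women separately", so each model has 350 people, about 175 per arm.

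The article names no residual correlation structure, no robust standard error and no between-visit correlation.

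**The concern.** A random intercept with ordinary independent residuals implies compound symmetry. Baseline and 12 months are then taken to be as strongly correlated as baseline and 6 months, with the same variance at every visit. The model applies one pooled variance to both change contrasts. If the true correlation is weaker across 12 months than across 6, that pooled figure understates the variance of the 12-month change.

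The 12-month contrast would then reject too often, giving a false SSUS benefit or a false K10 harm signal. The 6-month contrast may err the other way. That matters for K10 because the article reads non-significance as reassurance, and an inflated standard error makes a real rise in distress easier to miss.

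**Working it through.** **Inputs.** From the article: three visits, a random intercept, 350 per sex, 1:1 allocation, and 25% loss by 12 months (Sample size calculation). Assumed, because the article gives none: the correlations between visits, equal variances, and a two-sided 5% test. The article has no figure of its own to reproduce on this point.

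**Formula.** Let r01, r12 and r02 be the baseline–6, 6–12 and baseline–12 month correlations. With complete data and equal variances, the random-intercept fit estimates their mean, rbar = (r01 + r12 + r02)/3. The ratio of model SE to true SE is then

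- 6-month change: sqrt[(1 − rbar)/(1 − r01)]
- 12-month change: sqrt[(1 − rbar)/(1 − r02)]

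and type I error = 2 × [1 − Φ(1.96 × ratio)].

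**Worked case**, r01 = r12 = 0.70, r02 = 0.50. Here rbar = 1.90/3 = 0.633. At 6 months the ratio is sqrt(0.367/0.30) = 1.11, type I error 3.0%. At 12 months it is sqrt(0.367/0.50) = 0.86, type I error 9.3%.

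**Range of assumptions.**

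| r01 / r12 / r02 | SE ratio, 6 m | SE ratio, 12 m | Type I, 6 m | Type I, 12 m |
|---|---|---|---|---|
| 0.60 / 0.60 / 0.60 | 1.00 | 1.00 | 5.0% | 5.0% |
| 0.60 / 0.60 / 0.55 | 1.02 | 0.96 | 4.6% | 5.9% |
| 0.60 / 0.60 / 0.50 | 1.04 | 0.93 | 4.1% | 6.8% |
| 0.65 / 0.65 / 0.50 | 1.07 | 0.89 | 3.6% | 8.0% |
| 0.70 / 0.70 / 0.50 | 1.11 | 0.86 | 3.0% | 9.3% |
| 0.55 / 0.65 / 0.50 | 0.98 | 0.93 | 5.4% | 6.8% |
| 0.50 / 0.70 / 0.40 | 0.97 | 0.88 | 5.8% | 8.4% |

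Whenever r02 is the smallest of the three, rbar exceeds it and the 12-month SE is too small. The direction at 6 months depends on whether rbar lies below or above r01. In the last two rows the follow-up visits correlate more strongly with each other than baseline does with 6 months, and the 6-month SE is slightly too small as well.

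**Check with dropout.** A REML random-intercept fit was simulated 6,000 times (175 per arm, 25% missing at 12 months, an assumed 15% at 6 months). Type I error at 6 and 12 months was:

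- 0.6/0.6 (equal correlations): 4.7% and 5.3%
- 0.6/0.5: 4.3% and 6.7%
- 0.7/0.49: 2.9% and 9.4%

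The closed form gives 4.1% and 6.8% for the second case and 3.0% and 9.5% for the third, so dropout does not change the picture.

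**Other readings of the model.** Suppose only the two follow-up visits are modelled, with a random intercept and correlations from 0.6/0.36 to 0.8/0.64. The SE ratios are 1.14 to 1.18 (6 months) and 0.88 to 0.90 (12 months) for change scores. With baseline as a covariate they are 1.08 to 1.15 and 0.90 to 0.93.

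**Cost in power at 6 months.** With a ratio of 1.11, a K10 difference that would have 80% power with the correct SE has Φ(2.80 − 1.96 × 1.106) = Φ(0.63), about 74%.

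**Overall test.** For 0.70/0.50, the 2-df group-by-time Wald statistic is distributed as 0.64 and 1.36 times two independent 1-df chi-squares. The weights average 1, so its type I error is about 5.5% (5.4% in a simulation with 131 per arm).

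**The case against.** The strongest reply is that the article does not say the random intercept stands alone. It states neither independent residuals nor a method for standard errors, and a random intercept can be combined with a structured residual or robust standard errors. An analysis plan not shown may do that. This stands as a limit: compound symmetry is the natural reading of the named model, but it is not stated outright. The point survives because it concerns a method the article chose to name, not a missing detail.

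Second, no document figure shows that an error will occur. Every correlation above is assumed, and mild decay gives only 5.9% at 12 months. This also stands, and it is why the conclusion is conditional.

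Third, the overall group-by-time test is a standard mixed-ANOVA test of differential change and is nearly unaffected. That is true, but the article words its safety expectation by visit, and the visit-level contrasts are where the error lies.

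Two stronger readings are tempting and should be resisted:

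- A reader might infer that fading correlation always makes the two standard errors wrong in opposite directions. That needs roughly equal adjacent-visit correlations. Disclosure and the mailed package fall between baseline and 6 months (Intervention and control), so the two follow-ups could well be closer to each other.
- A reader might infer that the trial is sized on the 12-month change. The Sample size calculation uses another trial's SSUS difference ("by a mean of 2.6 points, effect size d = 0.40"); 12 months enters only through the 75% response rate used for inflation.

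**Conclusion.** The point holds as a conditional weakness of a named method. Read naturally, the model assumes equal variances and equal correlations across the three visits, an assumption the article neither states nor supports with data.

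If correlation falls with the time gap, and variances are about equal, the 12-month change contrast is too liberal: about 6% under mild decay (0.60/0.55) and about 9% under stronger decay (0.70/0.50). The 6-month contrast is then conservative (4.6% down to 3.0%) when adjacent-visit correlations are similar. Otherwise it may be about right or slightly liberal (5.4% in the 0.55/0.65/0.50 case). Unequal variances would change these sizes.

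The 9% figure is the upper end of an assumed range, not an estimate of this trial's error rate. With equal correlations there is no error. This is a worthwhile, cheap improvement and not a flaw that invalidates the design.

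**What to change.** In the Statistical analysis section, replace the random intercept for SSUS, K10 and days off work with an unstructured covariance across baseline, 6 and 12 months. Fit it by REML with Kenward-Roger degrees of freedom, and report the group differences in change at 6 and at 12 months from that model.

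Each change contrast then has its own variance, so type I error returns to about 5% whatever the correlation pattern. Compound symmetry is contained as a special case, and people with partial follow-up still contribute.

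The cost is a sentence of text and a few extra covariance parameters (six in place of two), well supported by about 350 participants per sex. The change should be recorded before outcomes are compared by group.
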